### Completion of baseline assessment

The following baseline assessments will be completed at visit 2:

1. Current medications and therapies (including complementary and alternative treatments)

2. The CDC criteria for CFS [1]

3. The London criteria for myalgic encephalomyelitis [40]

4. Presence or absence of fibromyalgia (using chronic widespread pain criteria only and not tender points) [41]

5. Preferred treatment group (single question)

6. The Client Service Receipt Inventory (CSRI), adapted for use in CFS/ME [42]

7. The self-paced step test of fitness [43]

8. The Borg Scale of perceived physical exertion, scored once immediately after the step test [44]

9. The actigraphy watch will be removed and the actigraphy data [18] (as initiated at visit 1 with the research nurse) will be downloaded.

### Randomisation and Enrolment procedure

Participants will be allocated to one of the four trial arms (ratio 1:1:1:1) by the Mental Health & Neuroscience Clinical Trials Unit (MH&N CTU) based at the Institute of Psychiatry. Allocation will be stratified by *centre*, *CDC Criteria *(met or unmet), *London Criteria *(met or unmet) and *depressive disorder *(major, minor depressive episode and dysthymia being present or absent) using minimisation with a random component [45]. The stratification on these criteria is to ensure equal proportions in each treatment arm. The first N cases (N will not be disclosed) will be allocated using simple randomisation to further enhance allocation concealment.

Once an eligible participant has completed the baseline assessment and given written informed consent, the RN will contact the MH&N CTU for treatment allocation by facsimile, giving the criteria needed for randomisation. Minimisation is carried out with a random component using a customised Microsoft Access database which will be used to hold the basic details collected to facilitate subsequent verification and to generate the allocation. Allocation is concealed because an independent group are responsible for this allocation. The confirmation of stratification details and treatment allocation will be communicated by email or facsimile to the RN within 24 hours. The RN sends back an acknowledgement of receipt to the CTU. This whole procedure is kept independent and separate from the trial statisticians. The RN will on the same day inform the participant of his/her treatment group in person or by phone, and will also inform the SSMC doctor and appropriate therapist. The therapist will contact the participant to arrange the first treatment appointment as soon as possible (within 5 working days). The SSMC doctor will also arrange to see the participant within one month of treatment allocation. The individual assignments will be available to the local team on a need-to-know basis, with the exception of the trial statisticians.

### Participant Identification Number

The participant identification number (PIN) will be a five digit number whereby the first two digits denote the centre and the remaining three denote the participant number by centre allocated in order of the patient entering the screening phase. Therefore every patient who consents to baseline and eligibility assessment will have a PIN, but not all will be randomised due to some being ineligible or not giving further consent.

### Randomised treatments

Apart from those receiving SSMC alone, all participants will be offered equal therapist time; 90 minutes in the first session, and 14 subsequent sessions of 50 minutes. The 15^th ^session will be a "booster" session given at week 36, thirteen weeks after the 14^th ^session, itself given at 23 weeks, which will be the last week for therapy. Therapy sessions 2 to 15 need not last the full 50 minutes if not required. If both therapist and participant believe that the next planned session is redundant because therapy is going so well, the next session may be omitted, with a note made as to the reasons why.

If the participant is unable to attend an appointment in person (e.g. due to feeling too disabled or due to intercurrent ill-health), and this cannot be re-arranged within five working days, and if agreed by both the therapist and participant, this session may be held over the telephone either at the pre-arranged time or within five working days of the original appointment. If the session does not take place within this time, the visit will be recorded as a DNA (Did Not Attend). Ideally, no more than four sessions of the first 14 sessions should be held in this way, and they should not be sequential. However, we believe it would be better that the participant receives some therapy rather than none at all and this will be judged on a per-participant basis. For this reason, if the choice is between not holding a session and a telephone session, a telephone session will always be offered even if there already have been four telephone sessions. This policy is supported by the results of one RCT and an open trial having suggested that two of the therapies (CBT and GET) delivered by telephone sessions following a face to face initial assessment is efficacious [46,47]. The fifteenth session will be held face-to-face, if at all possible, but even this may be held by telephone if the alternative is non-attendance.

We have chosen 15 sessions for all supplementary treatments on the basis of the previous trials of CBT and GET [18,23-26], as well as extensive clinical experience. RCTs of the least effective CBT and GET trials used 6 and 8 sessions [25,48]. Although one study of a pragmatic rehabilitation found that only 4 sessions were helpful [47], we suspect that this result may have been related to the lack of a 'treatment as usual' control group, and that more than four sessions are necessary to achieve change. A two year follow-up of this trial showed that the maximal face-to-face intervention had better efficacy by this time [19]. All interventions will be based on manuals, revised following feedback from both patients and therapists after piloting the manuals and therapies on patients outside of the trial.

### Adaptive Pacing Therapy

*APT *will be based on the illness model of CFS/ME as a currently undetermined organic disease, with the assumption that APT can improve quality of life, although not affect the core disease, other than providing the best conditions for natural recovery. APT is essentially an energy management approach, which involves assessment of the link between activity and subsequent symptoms and disability, establishing a stable baseline of activity using a daily diary, with advice to plan and pace activity in order to avoid exacerbations. Strategies include developing awareness of early warning of exacerbations; limiting demands; regular planned rest and relaxation, and alternating of different sorts of activities. The aim is to achieve optimal adaptation to the illness [4,16,17]. The patient charity *Action for M.E. *have helped in the design of the APT manual and have endorsed this version of pacing, which is based on what is published and what patients and clinicians have reported as helpful. Both therapists and participants will receive separate manuals.

### Cognitive Behaviour Therapy

*CBT *will be based on the illness model of fear avoidance, used in the three positive trials of CBT [18,25,26]. There are three essential elements: (a) Assessment of illness beliefs and coping strategies, (b) structuring of daily rest, sleep and activity, to establish a stable baseline of general activities, with a graduated return to normal activity, (c) collaborative challenging of unhelpful beliefs about symptoms and activity. Both therapists and participants will receive separate manuals.

### Graded Exercise Therapy

*GET *will be based on the illness model of deconditioning and exercise intolerance, used in the previous trials [23,24,47]. Therapy involves an assessment of physical capacity, establishing a stable baseline level of physical activity, negotiation of an individually designed home exercise programme with set target heart rates and times, and participant feedback with mutual planning of the next fortnight's exercise programme. Both therapists and participants will receive separate manuals.

### Standardised Specialist Medical Care

*SSMC *will be given to all participants. This will include visits to the clinic doctor with general, but not specific advice, regarding activity and rest management, such as advice to avoid the extremes of exercise and rest, as well as pharmacotherapy for specific symptoms and comorbid conditions. SSMC is standardised in the SSMC Doctor's Manual. As well as this, SSMC participants, like all other participants, will already have received the Patient Clinic Leaflet (PCL). The PCL is a generic leaflet explaining what CFS/ME is, its likely causes, and available treatments. There will be no additional therapist involvement. In particular there will be no diary monitoring with consequent advice. The number of SSMC outpatient sessions will be recorded, along with any treatments given for each participant by the SSMC doctor. Participants will be seen by their SSMC doctor a minimum of three times after randomisation, with the first SSMC appointment taking place as soon as possible after randomisation, and within one month. Further sessions will be determined by clinical need. Trial therapists, participants and general practitioners can request an unplanned clinical review by the SSMC doctor.

### Departures from randomised treatment

We will use the following strategies to minimise missing data in primary outcomes. Participants who drop out of treatment will be assessed as soon as possible, rather than waiting for the normal follow-up. Those who cannot attend clinic will be offered home assessments by the RN (or failing this assessment by telephone or by post), or centre leader as appropriate. If that is not achieved, we will seek to obtain outcome data by use of either postal or e-mail questionnaires, supplemented by telephone calls if necessary.

### DNAs from treatment

The therapist (if they have one) or SSMC doctor will contact the participant by telephone in the first instance to ascertain the problem of attendance, and will discuss the appropriate solution with the participant. Choices include a telephone session or a re-arranged face-to-face session, so long as the latter is within five working days. Alternatively the session stays a DNA and is recorded as such. If the participant considers that they are deteriorating the policy for this problem will be enacted.

### Clinician/Researcher withdrawal of participant from treatment

The reason for this will be recorded. When this occurs, the centre leader or nominee should assess the participant clinically within a week, and arrange appropriate care. Every effort will be made to obtain the two primary outcomes and the CGI (to assess illness progression), which should be scored in order to provide some outcome data. Such participants' data will be included in the trial analysis. If the participant will still consent to research (RN) follow-up, this will continue as normal.

### Participant withdrawal of consent to randomised treatment

In the first instance, the therapist (if they have one) or SSMC doctor will contact the participant by telephone to ascertain the reason for drop-out, if the participant is willing to share this, and will discuss the appropriate solution with the participant and then the centre leader. If the participant considers that they are deteriorating, but does not wish to talk to the therapist or SSMC doctor, the centre leader or nominee should contact them themselves.

If possible, the reason for withdrawal (e.g. adverse events, intercurrent illness, illness progression, inability to adhere, inability to attend regularly for treatment or assessment) should be ascertained. This information will be passed on to the other relevant members of the team and the trial manager (TM). The centre leader will ensure that every effort is made to obtain the primary outcome measures and the Clinical Global Impression (CGI) change score [49] from participants who drop out of treatment as soon as this occurs, even if they are not dropping out of the trial follow-up itself.

The centre leader or nominee will also ascertain whether consent is withdrawn from further trial treatment only or from both trial treatment and follow-up and in the latter case, whether the participant has given permission to retain data collected before treatment withdrawal for use at final analysis.

### Participant withdrawal of consent to research follow-up

If a participant withdraws consent for research (RN) follow-up during the trial, the centre leader or nominee should be informed on the same day, if possible. The centre leader or nominee will then contact the participant to find out why the participant wishes to withdraw from research follow-up, if they are willing to give a reason. The centre leader or nominee will also determine whether the participant has given permission to retain data collected before withdrawal for use at final analysis, or whether this information should be destroyed. No data from the latter participant will be used in analysis.

### Loss to follow-up

Permission will be sought from the Office of National Statistics (ONS) in England and the Information and Statistics Division (ISD) in Scotland, to track all participants randomised using NHS numbers. If a participant is lost to follow-up, the participant's GP will be contacted in the first instance, and if the participant has moved from the area, ONS (or ISD) will be contacted for details of the participant's new GP. This will only occur if the participant has given explicit consent (as detailed on the consent form) to allow this.

In all these situations the centre leader should inform the general practitioner and any referring doctor that their patient has withdrawn from either the trial or the trial treatment.

### Measures of treatment compliance/adherence

The SSMC doctor will record how many clinic outpatient sessions were attended, and how many were not attended during the 52 weeks by reviewing the medical notes.

If the participant has been receiving supplementary therapy, the therapist will record how many sessions/part sessions out of 15 were attended; whether they were face-to-face or telephone consultations and the durations of each session attended. At the end of therapy, the therapist will also score how well the participant adhered to the general therapy approach.

### Modification of trial treatment

Trial treatments will only be modified with the advice of the TSC, having been advised by the DMEC that a particular treatment arm is causing a consistent pattern of deterioration, or if there is another obvious and significant clinical necessity. The MREC will also need to approve any change in treatment.

### Additional therapy after the trial

Participants who are judged to require further therapy after their involvement in the trial has been completed, will be offered additional therapy. The choice of additional therapy will be agreed by the participant, clinic doctor and relevant therapist, and will start after the final follow-up interview (52 weeks after randomisation into the trial).

### Absence of a therapist

There will be occasions throughout the course of the trial when a therapist is absent due to annual leave, sickness, maternity leave or resignation. In these instances treatment delivery will be modified in order that a participant's therapy and the trial may continue uninterrupted. Three contingency plans have been devised to allow for a flexible approach to tackling this situation when it arises.

#### Therapy from a nearby centre

Local centre cover is delivered by a PACE therapist of the same discipline working in a nearby PACE centre.

#### Distant combined therapy

Distant therapy is delivered by a PACE therapist of the same discipline, whereby the therapist will conduct some visits face-to-face and the remainder by telephone. The participant at the same time may also be treated by a local cross-cover PACE therapist.

#### Local cross-cover therapy

Cross-cover therapy is delivered by a PACE therapist of a different discipline, whereby the cross-cover therapist learns a second PACE therapy to a competent level. They are supervised both by a distant centre PACE therapist of the appropriate discipline and a local therapist of the same discipline providing emergency assistance and assessment in case the patient has an intercurrent problem (e.g. pulls a muscle during GET).

#### Recruitment of a new therapist

In the case of resignation or maternity leave, the collaborating centre will seek to recruit a replacement therapist as quickly as possible.

It is recognised that there is a shortage of therapists working in the NHS and for this reason, the recruitment of staff of alternative appropriately qualified disciplines may also be considered. For example, an exercise physiologist may be recruited in place of a physiotherapist to deliver GET. There have been two randomised controlled trials of GET for CFS/ME provided by exercise physiologists, with positive outcomes [23,50]. In these instances the therapist will operate as a 'physiotherapy assistant' to a supervising physiotherapist. Similar alternative disciplines and supervision arrangements may also be considered for APT and CBT.

#### Changes to consent process

If a participant is to receive treatment from a therapist of either a different centre or a different discipline, the participant will give additional informed consent once it is clear that they understand this and are willing to receive their treatment in this way.

### Assessments and Procedures

#### Assessments

All participants will usually be assessed at the hospital. Those participants who cannot attend clinic will be offered home assessments (or failing this assessment by telephone or by post). Before the second and consequent RN assessments, self-rated measures will be posted to the participant prior to the visit and checked for completion at assessment by the RN. If a participant becomes too tired or ill to continue with the assessment, they will be offered the opportunity to complete the assessment on another day, within the next seven days.

Because we do not think it practically possible for the RN to remain blind to treatment group allocation, we will not attempt to achieve this. All our primary and secondary outcomes are therefore either self-rated or objective in order to minimise observer bias. Participants who drop out of treatment will be assessed for outcomes as soon as possible, rather than waiting for the normal follow-up.

When the participant does not attend a research interview, the RN should send the self-rated questionnaires to the participant's home address, with a stamped addressed envelope. If questionnaires are not received back within a week, the RN should arrange to visit the participant at home and oversee completion of the questionnaires. If necessary, only the primary outcomes and the CGI [49] (to assess deterioration) should be the minimum completed.

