#### Adverse outcomes

Adverse outcomes (score of 5–7 of the self-rated CGI) will be monitored by examining the CGI at all follow-up assessment interviews [49]. An adverse outcome will be considered to have occurred if the physical function score of the SF-36 [28] has dropped by 20 points from the previous measurement. This deterioration score has been chosen since it represents approximately one standard deviation from the mean baseline scores (between 18 and 27) from previous trials using this measure [23,25]. Furthermore, the RN will enquire regarding specific adverse events at all follow-up assessment interviews.

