#### Non-serious adverse events and reactions

Non-serious adverse events or reactions will be assessed by the RN at each follow-up assessment interview. A risk assessment has been undertaken, and we have concluded that the therapies are of low risk to participants. Non-serious adverse events will be reported according to the usual regulatory requirements.

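### The minimum data set for a missed research interview contains no adverse event enquiry, so non-serious adverse events can be missed in participants who give only postal or minimum data

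*Protocol article*

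**What the plan says.** Routine enquiry about adverse events is described in two places in the protocol article, and both attach it to an interview. Adverse outcomes states that "the RN will enquire regarding specific adverse events at all follow-up assessment interviews". Non-serious adverse events and reactions states: "Non-serious adverse events or reactions will be assessed by the RN at each follow-up assessment interview".

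For a missed research interview, the Assessments section says that "the RN should send the self-rated questionnaires to the participant's home address, with a stamped addressed envelope". If they are not returned within a week, the nurse arranges a home visit to see them completed. The floor is then given: "If necessary, only the primary outcomes and the CGI [49] (to assess deterioration) should be the minimum completed".

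The same short set is named for people leaving treatment. Participant withdrawal of consent to randomised treatment asks that "every effort is made to obtain the primary outcome measures and the Clinical Global Impression (CGI) change score [49] from participants who drop out". The section on clinician withdrawal names the same measures.

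Other routes bear on harm:

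- Adverse outcomes defines deterioration through measures inside the minimum set: "Adverse outcomes (score of 5–7 of the self-rated CGI) will be monitored by examining the CGI", and a 20-point fall in SF-36 physical function also counts.
- The section on reporting SAEs and SARs requires a report as soon as the nurse or SSMC doctor learns of a serious event.
- The reason for withdrawal is sought where possible, with adverse events among the examples.
- The policy on deteriorating participants and treatment drop-outs provides a detailed clinical assessment, in the home where needed.

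**The concern.** The Abstract lists adverse events and reactions as secondary outcomes. Risks and benefits and Safety of participants both describe a conflict between patient surveys and published trials over harm from CBT and GET, so complete and even-handed ascertainment of harm matters more here than in most trials.

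A site that follows the Assessments section to the letter can close a missed visit with returned questionnaires and no adverse event enquiry. This is so even when the full questionnaire pack comes back, because the enquiry is the nurse's task at interview. If people miss interviews partly because they are unwell, the missing adverse event data are informative. If the share of postal or minimum-data participants differs between arms, the comparison of adverse event rates is distorted as well as the level.

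**Working it through.** **Step 1: what each route captures in a participant who misses the interview and gives only postal or minimum data.**

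| Information on harm | Captured? | Section |
|---|---|---|
| CGI 5 to 7 | Yes, the CGI is in the minimum set | Adverse outcomes |
| SF-36 physical function fall of 20 points | Yes, it is a primary outcome | Adverse outcomes; Primary outcome measures |
| Serious adverse event | Only if the nurse or SSMC doctor learns of it | Reporting SAEs and SARs |
| Adverse event as reason for leaving treatment | If possible, and only for withdrawal | Participant withdrawal of consent to randomised treatment |
| Other specific or non-serious adverse event | No stated route | Adverse outcomes; Non-serious adverse events and reactions |

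The last row is the gap. The Adverse Events section defines an adverse event broadly, covering any clinical change or disorder whether or not it is related to treatment. Two scales and a global rating cannot show what happened. Nor can they support the judgements of seriousness, relationship and expectedness that the reporting section requires.

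**Step 2: who is affected.** Leaving treatment is not leaving research follow-up. The section on clinician withdrawal lets nurse follow-up continue as normal with consent. The section on participant withdrawal wants the short set at drop-out even from those staying in follow-up. For these people it is an extra early assessment, and interviews with adverse event enquiry can still take place. The gap concerns those who give only postal or minimum data.

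**Step 3: scale.** The plan states no figure for this. Its drop-out allowance reproduces: 135 / (1 − 0.10) = 150 per arm, so 10% is 15 of 150. Let d be the share of an arm with no enquiry and m the adverse event risk in those not asked, relative to those asked. If no other route captures events in those not asked:

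share of cases missed = d·m / [(1 − d) + d·m]

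The values of m are assumptions. The values of d are borrowed from Power analyses (10% planned; 3% to 40% across the cited trials, 33% being the higher GET figure). Those are drop-out rates, not rates of missing enquiry.

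| d | m = 1 | m = 1.5 | m = 2 |
|---|---|---|---|
| 3% | 3% | 4% | 6% |
| 10% | 10% | 14% | 18% |
| 33% | 33% | 42% | 50% |
| 40% | 40% | 50% | 57% |

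For d = 10% and m = 2: 0.20 / (0.90 + 0.20) = 0.18.

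**Step 4: the denominator.** If only those asked are counted, recorded risk over true risk is 1 / [(1 − d) + d·m]. At d = 10% this is 1.00 for m = 1 and 1 / 1.10 = 0.91 for m = 2. The shortfall falls from 18% to 9% but does not vanish when risk is related to non-response.

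**Step 5: between arms.** With the same d and m in two arms, the ratio of recorded risks is unbiased. With m = 2, d = 3% in one arm and 10% in the other, the captured shares are 0.97 / 1.03 = 0.942 and 0.90 / 1.10 = 0.818. Two arms with equal true risk would then show a recorded ratio of 0.818 / 0.942 = 0.87. This split is illustrative.

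**The case against.** The strongest counter-argument is that a short fallback is deliberate and sensible: asking little of ill participants protects the primary outcomes. The set was also chosen with harm in mind, since the text gives assessment of deterioration as the reason for the CGI. The article is condensed as well, and the full protocol or case report forms may contain an adverse event form for postal and telephone contacts.

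Much of this stands, and it rules out several stronger readings that a reader might infer:

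- *That harm goes unrecorded in these participants.* Both parts of the protocol's adverse-outcome definition are in the minimum set.
- *That adverse events come to light only at interviews.* Serious events are reported whenever learned of, and adverse events are sought as a reason for withdrawal.
- *That all treatment drop-outs are affected.* Those who continue nurse follow-up are not.
- *That those affected are the people most likely to have been harmed, or that the between-arm difference would reverse direction.* The first is plausible but not stated. The second needs event rates and a drop-out split that the documents do not give.
- *That being too disabled to attend removes people from assessment.* That remark, under Randomised treatments, concerns therapy sessions. For research assessments, home, telephone or postal alternatives are offered.

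The condensed format does not remove the remaining point. The article is not silent: it states the minimum set and states where the enquiry takes place, and the two do not meet. The clinical assessment of drop-outs is described as care, with no stated link to the adverse event record. The serious-event route is passive, because it starts only when someone learns of the event.

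**Conclusion.** The point holds in a limited form. As written, ascertainment of non-serious adverse events, and of serious events not otherwise learned of, can be incomplete in participants who give only postal or minimum data. The incompleteness may be related to harm and may differ by arm.

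Its size cannot be derived from the documents. At 10% of an arm with no enquiry, 10% to 18% of adverse event cases would be missed for relative risks of 1 to 2. For those inputs this is an upper bound, because it assumes zero capture by any other route and treats every drop-out as never asked. A relative risk above 2 would raise it. None of these figures applies to deterioration measured by the CGI or SF-36.

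This is an inexpensive improvement to a secondary outcome that is central to the trial's question. It does not affect the primary analysis.

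**What to change.** - **Minimum set.** In the Assessments section, define the minimum as the two primary outcomes, the CGI and a brief standard adverse event and SAE enquiry. Ask it last, so that the primary outcomes and CGI remain protected, and use the postal, telephone or home contact already planned. Make the same addition in the two sections on withdrawal from treatment, for participants who will not continue nurse follow-up.
- **No contact.** Where contact fails and consent stands, check the medical notes for SAEs. Permission to review notes is already an eligibility condition (visit 1, item 10), and notes are already reviewed for attendance.
- **Reporting.** Give by arm the number of participants asked about adverse events at each assessment, the mode of enquiry, and the number never asked. Show adverse event rates with those asked as denominator as well as all randomised.

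The cost is a few questions in existing contacts and a change of wording in the protocol and case report form. The downsides are slight extra burden for unwell participants and mixed modes of enquiry, which reporting the mode by arm makes visible. If the full protocol already provides such an enquiry, it is enough to state this in the sections named.
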